The IBR-MOAS measures the frequency and severity of aggressive behavior episodes. The scale is divided into five subscales: (1) verbal aggression toward others, (2) verbal aggression toward self, (3) physical aggression against other people, (4) physical aggression against objects, and (5) physical aggression against self. Items are rated on frequency on a 5-point Likert scale: never=never happens, rarely=averages about once a year to once a month, sometimes=averages about several times a month to several times per week, often=averages about daily to several times a day, and U=used to happen but not in the past year. For our analyses, we will code U ratings as equivalent to never. Unlike the original Overt Aggression Scale and other modified versions, a weighted scoring system was not used. We will adapt the measure to include other challenging behaviors of interest (eg, escape, climbing furniture, and meltdowns). Participants will complete this measure at baseline and 3 months after baseline.

*Emotion dysregulation:* Emotion dysregulation will be measured through parent and teacher reports using the Emotion Dysregulation Inventory (EDI), either the original version [70-72] or the young child version [73], depending on the child’s age. The scales consist of 30 items (original version) or 22 items (young child version) for raters to indicate how much of a problem certain emotions and behaviors are for the individual, being rated on a 5-point Likert scale ranging from 0 (“Not at all”) to 4 (“Very severe”). The EDI produces scores for reactivity (rapidly escalating, intense, and poorly regulated negative affect) and dysphoria (sadness, low positive affect, and unease). Raw scores are summed and converted to standardized scores with clinically elevated cutoffs, based on a large autism sample, and scoring information from a US census–matched sample of 1000 youths provides clinical cutoffs. Participants will complete this measure at baseline and 3 months after baseline.

#### Technical Outcomes

*Artifact removal:* The total number of “artifacts”—interbeat HR intervals (also known as RR intervals) >200 ms [55] detected during the testing period will be calculated throughout study participation.

*Offline mode activations*: The proportion of time for which “offline mode” (refer to the Offline Mode section for more details) is activated over the testing week based on the accelerometry data threshold will be calculated throughout study participation.

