### Objectives

We present the framework and protocol for a pilot randomized waitlist-controlled field trial that aims to examine the implementation of a digital mental health app, the KeepCalm app (refer to the *Materials* section for details about the app), designed for children on the autism spectrum with challenging behaviors of any IQ or speaking ability. Given that >95% of digital mental health apps have not actually been studied [44,45], an overarching goal of the project is to test the KeepCalm app systematically. We expect the KeepCalm app to score high on usability, acceptability, feasibility, and appropriateness. We also predict satisfactory proximal efficacy (>80% clinical decision support success rates and <20% false positive and negative rates), high technical reliability (the removal of artifacts and offline mode activation success), and the use of the KeepCalm app to result in low severity and frequency of challenging behaviors and emotional dysregulation in children on the autism spectrum after the trial relative to baseline.

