### Materials

#### Overview of the KeepCalm App

The KeepCalm app is designed to be an interactive learning and data collection tool to facilitate a team approach to support emotion regulation in students. It integrates wearable HR tracking to identify and alert educators about heightened stress in their students and remind them about evidence-based strategies for de-escalating stress, supporting proactive coping, and preventing challenging behaviors. Refer to Figure 2 for the KeepCalm causal model, which shows that the pathway from stress to challenging behaviors via emotion dysregulation is “rescued” with the KeepCalm app, via teacher-assisted emotion regulation, whereby the teacher supports their student to reattain autonomic equilibrium (ie, physiological baseline or resting state) via stress communication (ie, child HR signaling to teacher), along with individualized recommendations about strategies to keep calm.

The KeepCalm app offers 3 innovations (to be tested) that address the 3 barriers described in the *Introduction* section (Figure 1). First, it incorporates physiological stress data into treatment delivery by capitalizing on recent advances in wearable biosensing [22,53,54]. The selected consumer-grade trackers are accurate [53,55,56] and have high technical reliability [55,57] for measuring HR (beats per minute) and HR variability (interbeat interval), making them inexpensive and scalable alternatives to medical-grade devices. In previous studies, we found that 85% of children on the autism spectrum will wear these trackers without complaint and rate them high on comfort and low on exacerbating sensory sensitivities [55,57].

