#### HR Stress Zone Tracking

The KeepCalm app pairs with selected commercially available HR trackers (refer to the *HR Trackers* section) that children wear to allow moment-by-moment physiological arousal tracking by educators. After recording a baseline HR for each child, educators are given pop-up notifications to alert them about moderate stress levels, along with individualized top strategies that can be used to reduce their stress. As HR is an index of stress levels [22-24], an increase in HR may index rising stress in children. HR above baseline (ie, HR at rest) is arranged in a stress zone rainbow in the KeepCalm app, with green representing baseline, yellow representing small increase in HR above baseline (+10%), orange representing medium increase in HR above baseline (+20%), and red representing large increase above baseline (+30%). Educators can track the child’s HR, so that they can intervene at moderate stress levels (ie, orange-zone HR) to prevent challenging behaviors associated with high stress levels or HR of approximately 30% above baseline [30] (ie, red-zone HR). In doing so, the educator creates emotion regulation learning opportunities for the child. Increase in HR may occur for other reasons, including increased physical exertion; however, accelerometry data movement thresholds ensure that increases in HR owing to child movement are not reflected in the HR stress zone tracking (refer to the *Offline Mode* section).

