#### HR Trackers

We will use 2 HR tracker models previously tested for accuracy, reliability, validity, and comfort [55]—the Mio Fuse (Mio Global) wristband and Polar H7 (POLAR) chest strap. These models are highly accurate (correlation with wired electrocardiogram: Mio Fuse: mean *r*=0.91, 95% CI 0.882-0.929; Polar H7: mean *r*=0.99, 95% CI 0.987-0.991) [53,56] and reliable (they meet quality thresholds on spike rate—Mio Fuse: 100%; Polar H7: 87.4%-89.4% and sampling fidelity—Mio Fuse: 96.2%-97.1%; Polar H7: 96.6%-100%) [55] for measuring HR and HR variability. We found that children on the autism spectrum rated both devices in the comfortable range [55], and in our pilot study, they were able to wear one of the 2 HR trackers during 5 school days.

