#### Secondary Outcomes

To examine technical reliability, we will use descriptive statistics of artifact removal success and offline mode activations. To examine proximal preliminary efficacy, we will use descriptive statistics of clinical decision support success rates and false positive and negative rates. To examine distal preliminary efficacy, we will also conduct a preliminary examination of the efficacy of KeepCalm on challenging behavior (SSQ and IBR-MOAS) and emotion dysregulation (EDI) using an exploratory (underpowered) repeated measures ANOVA to assess the 2 groups (waitlist and treatment) at baseline and posttrial periods. Given the sample size, this analysis will be underpowered.

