#### Power

For the study’s pilot randomized controlled trial, the analyses will focus on feasibility, usability, and implementation (descriptive) data but will include some preliminary efficacy inferential analyses. In this study, 50% (10/20) of the teams will be randomized to the treatment condition and 50% (10/20) of the teams will be randomized to the waitlist control condition. The sample size was not based on power analysis but rather a need to obtain pilot data that will support an app for a fully powered trial.

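### The artifact outcome counts RR intervals above 200 ms, which as written takes in nearly every genuine heartbeat, and a raw total cannot show artifact removal success

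*Protocol article*

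**What the plan says.** The article deals with artifacts in four places.

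- **Technical Outcomes** gives the only definition. The outcome is the total number of artifacts, described as "interbeat HR intervals (also known as RR intervals) >200 ms [55] detected during the testing period will be calculated throughout study participation".
- **Objectives** predicts "high technical reliability (the removal of artifacts and offline mode activation success" among its components.
- **Data Analysis, Secondary Outcomes** states that "we will use descriptive statistics of artifact removal success and offline mode activations".
- **Table 1** lists artifact removal success under technical reliability, taken from app data during the 3-month trial.

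The abstract also names the number of artifacts as a technical outcome, collected with others in preparation for a fully powered trial.

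The companion outcome in Technical Outcomes is the proportion of time for which offline mode "is activated over the testing week based on the accelerometry data threshold".

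**The concern.** The parenthesis in the definition equates the quantity being thresholded with the RR interval itself. The limit therefore applies to the length of an interval, not to a change between intervals, and it has no upper bound. A rule meant to pick out faulty intervals instead picks out ordinary ones and passes over implausibly short ones.

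There is a second mismatch. A count of artifacts is defined, but removal success is to be analysed. A count says nothing about how many artifacts were removed, and it rises with the number of hours the tracker is worn.

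What is at stake is whether this outcome can be used when planning the later trial. Coded literally, it would be a beat count under another name. If analysts quietly apply a different rule, the reported outcome will not be the published one.

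**Working it through.** **Inputs from the article.** The threshold is an RR interval above 200 ms (Technical Outcomes). Heart rate is in beats per minute and the interbeat interval is the time between beats (Overview of the KeepCalm App). The top stress zone is 30% above resting baseline (HR Stress Zone Tracking). The article gives no artifact count or rate, so there is no stated figure to reproduce.

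**Assumptions, not in the article.** Resting baselines of 80 to 110 bpm, a 6-hour school day, and normally distributed RR intervals with the SDs shown below.

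**Step 1: threshold as a heart rate.** RR (ms) = 60,000 / HR (bpm). Setting RR = 200 gives HR = 60,000/200 = 300 bpm, so any beat below 300 bpm has an interval above 200 ms.

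| HR (bpm) | RR (ms) | Counted as artifact |
|---|---|---|
| 60 | 1000 | yes |
| 80 | 750 | yes |
| 120 | 500 | yes |
| 160 | 375 | yes |
| 200 | 300 | yes |
| 220 | 273 | yes |
| 300 | 200 | no |

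**Step 2: the app's own top zone.** From a baseline of 80 bpm, RR = 60,000/(80 × 1.3) = 577 ms. From 110 bpm, RR = 60,000/(110 × 1.3) = 420 ms. Both are counted.

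**Step 3: allowing for beat-to-beat variation.** The share flagged is 1 − Φ((200 − mean RR)/SD).

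- Mean HR 70 to 130 bpm, SD up to 100 ms: lowest at 130 bpm and SD 100, where mean RR = 461.5 and the share is 99.5%.
- Mean HR 160 bpm: 99.8% at SD 60 and 96.0% at SD 100.
- Mean HR 200 bpm: 95.2% at SD 60 and 84.1% at SD 100. These are extreme settings for a school day.

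**Step 4: size of the total.** Beats per day = HR × 60 × 6. At 90 bpm this is 90 × 60 × 6 = 32,400. At 80 and 120 bpm it is 28,800 and 43,200. A child who wears the tracker for half the day at 90 bpm gives 32,400/2 = 16,200. The count halves with no difference in signal quality.

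**Step 5: one possible intended rule, for illustration only.** Suppose 200 ms referred to the absolute difference between successive RR intervals. With lag-1 correlation ρ, the SD of the difference is SD × √(2(1 − ρ)), and the share flagged is 2(1 − Φ(200/SD of difference)).

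- SD 60, ρ = 0: the difference has SD 84.9, and 1.8% is flagged. With SD 30 to 60 and ρ from 0 to 0.8, the range is about 0% to 1.8%.
- SD 100: 16% at ρ = 0 and 0.2% at ρ = 0.8.

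That rule would behave far more like an artifact detector, but the article does not state it. At high variability it could also flag a sizeable share of valid beats.

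**The case against.** The strongest reply is that this is a slip of wording. The definition cites reference 55. The HR Trackers section cites the same evaluation for device reliability: "they meet quality thresholds on spike rate—Mio Fuse: 100%; Polar H7: 87.4%-89.4" per cent. A team reporting such figures is unlikely to run a rule that rejects nearly every beat. That is plausible, although the article does not define spike rate, so the two measures cannot be equated. The sentence still states a specific rule that does not work, and no other section replaces it.

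A second reply is that denominators and breakdowns by device are details an article may leave to the full protocol or analysis plan. That is fair as far as it goes. What remains is that the article fixes the outcome as a total and then names a different quantity for analysis.

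Three stronger readings are tempting, and the article does not support them.

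- **That heart rate data for alarms, or for false positive and false negative scoring, would be lost.** Nothing says this rule filters the live heart rate stream. Alerts depend on heart rate relative to a recorded baseline and on the accelerometer-based offline mode. False positives and negatives come from classroom observation and app data entry.
- **That the intended rule is known to be a successive difference.** The cited source is not at hand, and the article never mentions differences.
- **That the offline-mode window truly conflicts with the design.** The same sentence says the proportion is calculated throughout participation, and Table 1 places it in the 3-month trial period. The week is a stray phrase, possibly carried over from the 5-school-day pilot.

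**Conclusion.** The concern holds as a narrow error. The stated rule classifies essentially all genuine beats as artifacts: at least 99.5% at mean heart rates of 70 to 130 bpm with RR SD up to 100 ms. The core result rests only on a unit conversion and on children's heart rates staying below 300 bpm. The daily count of about 32,400 also depends on the assumed 90 bpm and 6 hours. Separately, a raw total mainly tracks wear time and cannot support or refute the reliability prediction in the Objectives.

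The consequence is limited. This is one of two technical outcomes and is reported descriptively. The primary outcomes are surveys and interviews, and the only inferential analysis is an exploratory ANOVA on behavior and dysregulation scales. None of these uses artifact counts. The definition should be corrected before analysis, but the trial's main conclusions do not depend on it.

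**What to change.** 1. Restate the artifact definition in Technical Outcomes so that it matches the rule actually used in the cited tracker evaluation. It may be a change of more than 200 ms between successive RR intervals, but the authors must confirm this before adopting it.
2. Replace the total with artifacts as a percentage of recorded beats, and give the percentage of artifacts removed, per child and per device model. Use the same quantity in the Objectives, Table 1 and the analysis section.
3. As a minor wording correction, replace the testing week in the offline-mode sentence with the 3-month testing period.

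The cost is a few words in the protocol and a line of analysis code. No new data are needed, provided the recorded interval data are kept.

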#### Adverse Events

We will use a brief Adverse Events Checklist to be administered to teachers and parents in the treatment group weekly throughout the trial, which may include items related to teachers experiencing stress triggered by monitoring their student’s stress levels. This checklist will be reviewed by the expert advisory board for the study before trial commencement.

### Ethics Approval

The trial is approved by the University of Pennsylvania institutional review board (829690) and the School District of Philadelphia research review committee (2022-12-1071).

### Procedure

The trial is registered at ClinicalTrials.gov (NCT05277194). After screening for eligibility, the 20 teams (at a minimum, teachers-parents and child dyads; at a maximum, teachers-parents and child-aide [or other educational team member] triads) will be randomized to the waitlist (n=10, 50%) or treatment group (n=10, 50%). The treatment (and later, the waitlist) group will use the app for 3 months. After a dyad or triad has signed up for the study, participants will complete a conferencing software-based intake meeting, during which they will be individually briefed about the KeepCalm app and complete the baseline assessments.

School personnel will then complete an in-app training session either remotely or in the classroom, during which they will receive access to the KeepCalm app, HR tracker, and accelerometer. The research team will also show or instruct teachers about how to put the HR tracker and accelerometer on the child or assist or instruct the child in putting them on themselves. Participants will download the app onto their own phones or, if they do not have an iPhone, an iPhone will be lent to them for their participation in the project. A member of the research team will also help the school personnel to customize the app for their student by showing them how to add the child’s profile and their triggers, behaviors and skills, and strategies. Standard but editable lists will be programmed into the app for each student, including evidence-based proactive and reactive strategies for reducing challenging behaviors and supporting emotion regulation [64]. All teachers recruited will have had professional development and in-class coaching in these strategies by coaches in our center. The research team will administer a fidelity assessment tool to teachers to understand their proficiency in implementing these strategies and provide additional coaching or resources for strategies, as needed.

Following this training, school personnel participants will begin testing the app within the classroom. They will initially record at least one baseline HR of the child, which will be used to calibrate the app’s stress zone notifications for the child. Baseline HR is recorded over a 5-minute period, during which the child will be engaged in a relaxing activity. We recommend that teachers take 2 to 3 baseline measurements to ensure accuracy. Students will then wear the HR tracker and accelerometer each day during the 3-month testing period. School personnel will be able to track the student’s HR and movement; enter child data about triggers and antecedents, challenging behaviors and skills, and intervention strategies; view the daily report; export the child’s data; and message others on the student’s team. School personnel will receive SMS text message support from the study team during the testing period and will be able to ask questions and troubleshoot any issues that arise during this period. Parents will be able to view the autogenerated daily report for the child, export and build figures of the child’s data, access the intervention strategy resources, and use the app’s messaging features. The research team will remotely monitor each participant’s use of the app during their respective testing period.

Following the app testing period, teachers, aides, and parents will provide feedback about their experience with the app during a brief interview with a member of the research team that will cover various themes including usability, acceptability, feasibility, appropriateness, and any adverse event that may have occurred (the latter will be in addition to the previously mentioned Adverse Events Checklist that will be administered weekly throughout the trial). Measures will be taken at eligibility determination, baseline, throughout the trial, and after the trial as per Table 1. A demographic survey will also be administered at baseline, including a question on the child’s current medications, as some are known to affect HR. If possible, given the COVID-19–related school policies and teacher preferences, the research team will perform in-class observations to obtain a first-hand look at the use of the KeepCalm app in the classroom and to track clinical decision support success and false positives and false negatives (as described in the *Measures* section).

**Table 1 table1:** Timeline for data collection.

Construct and measure			Respondent or assessor		Timeline												
					Baseline					Throughout the trial (3 months)					After the trial		
					WL^a^		TX^b^		WL			TX		WL			TX
**Eligibility**																	
	SCQ^c^	Parent		✓		✓											
**IQ**																	
	Any standardized IQ battery, as reported on the child’s IEP^d^ (if not available, Stanford Binet ABIQ^e^)	Investigator, if required		✓		✓											
**Primary outcome measures**																	
	SUS^f^ (usability)	Teacher and parent														✓	
	AIM^g^ (acceptability)	Teacher and parent														✓	
	FIM^h^ (feasibility)	Teacher and parent														✓	
	IAM^i^ (appropriateness)	Teacher and parent														✓	
	Qualitative interview	Teacher, aide, and parent														✓	
**Technical reliability**																	
	Artifact removal success	Investigators (app data metrics)									✓						
	Offline mode activations	Investigators (app data metrics)									✓						
**Proximal preliminary efficacy**																	
	Implementation success	Investigators (classroom observation)									✓						
	False positives and false negatives	Investigators (classroom observation)									✓						
**Distal preliminary efficacy**																	
	SSQ^j^ (CB^k^ severity)	Teachers		✓		✓							✓			✓	
	OS-CBS^l^ (CB severity)	Parents		✓		✓							✓			✓	
	IBR-MOAS^m^ (CB frequency)	Teachers and parents		✓		✓							✓			✓	
	EDI^n^ (dysregulation)	Teachers and parents		✓		✓							✓			✓	
**Adverse events**																	
	Adverse events checklist	Teachers and parents									✓					✓	

^a^WL: waitlist group.

^b^TX: treatment group.

^c^SCQ: Social Communication Questionnaire.

^d^IEP: Individual Education Program.

^e^ABIQ: Abbreviated Battery IQ.

^f^SUS: System Usability Scale.

^g^AIM: Acceptability of Intervention Measure.

^h^FIM: Feasibility of Intervention Measure.

^i^IAM: Intervention Appropriateness Measure.

^j^SSQ: School Situations Questionnaire.

^k^CB: challenging behavior.

^l^OS-CBS: Open-Source Challenging Behavior Scale.

^m^IBR-MOAS: Institute for Basic Research Modified Overt Aggression Scale.

^n^EDI: Emotion Dysregulation Inventory.

### Data Analysis

#### Primary Outcomes

This trial is designed to test usability, acceptability, appropriateness, and feasibility data rather than efficacy; therefore, primary outcome data analyses will use descriptive statistics of the survey measures on usability (System Usability Scale), acceptability (Acceptability of Intervention Measure), feasibility (Feasibility of Intervention Measure), and appropriateness (Intervention Appropriateness Measure) of the KeepCalm app, as outlined in the *Measures* section.

We will also examine usability, acceptability, feasibility, and appropriateness through a qualitative interview and examine barriers to and facilitators of using the KeepCalm app in classrooms with students on the autism spectrum. Audio recordings of the interviews will be transcribed, and all transcripts will be loaded into Dedoose for data management and analysis. Thematic analysis will be guided by an integrated approach that includes identification of a priori attributes of interest (usability, acceptability, feasibility, and appropriateness). This integrated approach uses an inductive process of iterative coding to identify recurrent themes, categories, and relationships in qualitative data. After exploring the data, a comprehensive coding scheme will be developed and applied to produce a descriptive analysis. A team of coders will separately code the transcripts and compare the results to assess the reliability of the coding scheme. Any disagreements in coding will be resolved by team consensus. After the coding scheme is finalized, coders will be required to code 2 transcripts in a row at a high level of agreement with the lead coder (*k*>0.70) before independent coding of the rest of the transcripts. Following this, the lead coder will code 20% of the transcripts in duplicate for the reporting of interrater reliability.

Quantitative and qualitative data about usability, acceptability, feasibility, and appropriateness will be integrated by examining the qualitative data from the participants who responded in the lowest versus highest quartile on the quantitative measures of each construct. Data analysis will inform our understanding of the usability, acceptability, feasibility, and appropriateness of the KeepCalm app and will provide a list of feature updates to be included in the app before the following fully powered randomized controlled trial.

